#### Measures

The primary outcome measure is total cholesterol at 12-month follow-up. A blood sample will be collected at baseline using usual GP practice equipment and procedures. Bloods are normally taken by the practice nurse or HCA and sent to the local NHS hospital Trust laboratory for analysis. Results are then received electronically through the participant’s medical record. The blood test will be repeated at 6 and 12-month follow up by a clinical research network nurse and processed using usual GP practice procedures described above.

The baseline data described below will be collected either directly from participant interviews/clinical measures or from the GP practice medical records.

#### Demographics

Demographic data including age, sex, marital status, employment status, ethnicity, Townsend deprivation score calculated using each participant’s postcode, mental healthcare worker details, whether or not the participant is on the Care Programme Approach (CPA), and whether they have a support worker or carer will be collected for each participant.

#### Clinical measures

Clinical measures including blood pressure, HbA_1c_ and lipids (HDL, Total/HDL ratio and LDL) will be measured using usual practice procedures. Other clinical measures include waist circumference, 10-year CVD risk scores (QRisk) [41], Framingham re-estimated on the UK population [42], and the PRIMROSE CVD risk prediction model [42], BMI, physical co-morbid conditions, and diagnosis of SMI confirmed by the GP practice medical record.

We will also ask participants at the baseline assessment if they would consent to providing a saliva sample for storage at UCL laboratories or collaborating centres in the UK and internationally for future genetic research. This will be used to determine whether there is any DNA variation relevant to mental health diagnosis and physical health outcomes. Participants will be given the opportunity to opt out of providing this saliva sample if they wish. It will not affect their entry into the trial.

#### Behavioural measures

CVD risk-lowering behaviours will be assessed through a validated self-report questionnaire on physical activity (IPAQ) [43] and validated researcher administered questionnaires on dietary intake (DINE) [44] and alcohol use (AUDIT-C) [45]. Each participant will also be asked their smoking status, and, if they are a current smoker; how many cigarettes they smoke a day.

The Morisky Scale of Adherence (MMS), a validated self-report questionnaire [46] will be completed twice at each time point by each participant. Participants will first be advised to complete the questionnaire while thinking about their psychiatric medications (for example, antipsychotics and mood stabilisers) and secondly in relation to any CVD risk-lowering medications they are currently prescribed (for example, statins, anti-hypertensives and/or stop smoking aids).

#### Quality of life and wellbeing

Quality of life will be measured through the EQ-5D-5 L, a validated self-report questionnaire [47], Well-being will be assessed using the self-report Warwick Edinburgh Mental Wellbeing Scale (WEMWEBS) [48].

#### Economic measures

Economic measures will be collected from the medical records at baseline and 12-month follow-up, including medications used in the 12-months prior to baseline and any new prescriptions during the study follow-up period. General and psychiatric hospital admissions, Accident and Emergency (A&E) contacts, outpatient visits, primary care contacts and community service use in the previous 12 months will all be collected from the medical records. In addition, participants will self-complete an adapted Client Service Receipt Inventory (CSRI) to collate additional information on service use, which is unlikely to be recorded in the medical records (for example, informal care arrangements, living situation, CVD risk-lowering service use external to the NHS, such as weight-management programmes, gym and leisure activities, and community service use [49].

#### Follow-up assessments

Follow-up assessments will be conducted at 6 and 12 months and will include all clinical measures, behavioural measures, quality of life and economic measures. At 12 months, we will additionally collect information on adherence to the PRIMROSE intervention appointments and client satisfaction using the Client Satisfaction Questionnaire - (CSQ) [50].

A table summarising all outcome measures and data collection time points can be found in Table 1.

**Table 1 Tab1:** Summary of baseline and follow-up measures

Measure	Source data	0 mth	6 mth	12 mth
1. Clinical measures				
Total cholesterol (mmol/l)	Blood test	✓	✓	✓
HDL, LDL, Total cholesterol/HDL ratio (mmol/l)	Blood test	✓	✓	✓
HBA1c (mmol/mol, %)	Blood test	✓	✓	✓
Systolic and diastolic blood pressure (mm/hg)	Clinical assessment	✓	✓	✓
2. Anthropometric measures				
BMI (kg/m^2^)	Clinical assessment	✓	✓	✓
Waist circumference (cm)	Clinical assessment	✓	✓	✓
3. Behavioural measures				
Alcohol intake (AUDIT-C)	Researcher administered questionnaire	✓	✓	✓
Smoking status	Researcher administered questionnaire	✓	✓	✓
Diet (DINE)	Researcher administered questionnaire	✓	✓	✓
4. Medical records.				
Active physical health conditions	Medical records	✓		✓
Service use (inpatient hospital stays, outpatient appointments, accident and emergency attendances, community service use, health checks and action plans)	Medical records	✓		✓
Prescribed medications	Medical records	✓		✓
CVD risk scores	Medical records	✓		✓
Scheduled appointments not attended	Medical records	✓		✓
5. Patient questionnaires				
Service use: Employment, Housing, Health and Leisure (EHHaL)	Patient self-report questionnaire	✓	✓	✓
International Physical Activity Questionnaire (IPAQ)	Patient self-report questionnaire	✓	✓	✓
Quality of life: EQ-5D-5 L	Patient self-report questionnaire	✓	✓	✓
Wellbeing: The Warwick-Edinburgh Mental Well-Being Scale (WEMWBS)	Patient self-report questionnaire	✓		✓
Morisky Scale of Adherence (MMS): Psychiatric medications	Patient self-report questionnaire	✓	✓	✓
Morisky Scale of Adherence (MMS): CVD preventative medications	Patient self-report questionnaire	✓	✓	✓
Client Satisfaction Questionnaire - CSQ	Patient self-report questionnaire	✓	✓	✓

### Statistics and data analysis

#### Sample size

A total of 350 people from 70 GP practices will be recruited in to the study. In determining the size of the trial, we considered 1) important effect sizes, 2) size of clusters, and 3) attrition.

#### Effect size

Our primary outcome is total cholesterol. Two community studies of UK adults with SMI reveal mean total cholesterol levels of 5.4 mmol/l (standard deviation (SD) 1.3) [14] and 5.7 mmol/l (SD 1.4) [51].

We consider an effect size of 0.4 SDs difference in cholesterol, between the two trial arms, to be the minimum clinically important difference. Statins usually have far greater effect sizes, approaching two SDs [52], however in this effectiveness trial, we are comparing a behavioural intervention with treatment as usual, so cannot expect effects as large as this. Based on a two-sample t-test, to detect a difference of 0.4 x (1.3 mmol/l) requires 132 participants per arm, with 90 % power and 5 % significance level.

#### Sample size inflation for clustering and attrition

To account for the cluster effect, we have assumed that five participants on average will be recruited per practice. Dropout rates in the SMI trials are <20 % at 12 months [30, 53]. Using an intra-class correlation coefficient of 0.02 for trials in primary care [54] and an average cluster size of four participants per practice (after allowing for 20 % attrition) yields 140 participants per arm. Inflating this figure for 20 % attrition and rounding up results equates to a total of 350 participants and 70 GP practices for the trial.

#### Statistical analysis

All analyses will be on an intention-to-treat basis. Statistical analyses will be carried out using Stata [55]. We will produce summary statistics for all variables, both overall and by randomised group. Summary statistics for continuous variables will be mean or median, (with SD, or interquartile range) as appropriate, and for categorical variables, frequency and percentage within each category.

The primary outcome will be analysed using a linear random effects regression model adjusting for the baseline cholesterol, whilst accounting for clustering as a random effect (GP practice). Results will be presented as mean difference between randomised arms with 95 % confidence interval and *P* value.

Appropriate analogous random effects regression models will be used to analyse the secondary outcomes.

For both the primary and continuous secondary outcomes, the residuals will be checked for normality. If they are not normally distributed, outcomes may be transformed. If it is necessary to categorise outcomes, it will be done with clinical input.

Complete case analyses will be the main analyses from this study. Bias due to missing data will be investigated. A supportive analysis will include adjusting for predictors of missingness that are related to outcome, if necessary, and adjusting for factors that have baseline imbalances that are related to the outcome. If the proportion of non-adherence is greater than 5 %, an appropriate analysis accounting for non-adherence will be considered. Those in the treatment-as-usual practices will be assigned an adherence score equivalent to no adherence to the intervention. If it is appropriate to carry out this analysis, it will be done once the statistician has been unblinded to randomised group. Results from the analysis of secondary outcomes and supportive analyses will be presented as estimates with 95 % confidence intervals.

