#### Consent and research assessments

Initial agreement to be contacted by a researcher from the local clinical research network will be obtained from individuals either at their screening appointment with the practice nurse/HCA or through the return of a reply slip to the GP practice sent to people who are already potentially eligible. If an individual does not respond to this letter, the GP practice will call them and ask whether they would be interested in receiving further information about the study from a research nurse. The researcher will then telephone each eligible and interested person to explain the study in detail and to determine whether they want to take part or not, answer any questions and arrange to obtain full written consent and a full baseline assessment. It will be explained that the individual is free to withdraw from the study at any time without having any effect on their care. If a participant is randomised to the intervention group and no longer wishes to attend the intervention appointments, he/she will still be invited to attend the follow-up assessments.

Written informed consent will be obtained from each participant before the baseline assessment begins. Baseline data will be collected by the researcher from the participant’s medical records and through interviews and participant self-complete questionnaires with all recruited participants at the start of the study. Outcome data will be collected at 6 and 12 months during the trial period. Participants will be allocated a unique study identification number, and data will be entered anonymously by researchers using a web-based system set up by Sealed Envelope [33]. It has range checks, consistency checks and for closed questions gives a number of options plus “other” where appropriate. Researchers who will be entering the data will have no access to the group allocation through this system. With these checks in place, there should not be any issues with illegal values or inconsistent data being entered, so necessary cleaning should be minimal. Data will be checked by the trial statistician before analysis and any problems reported to the trial manager, who will liaise with the researchers to rectify them as appropriate before data analysis.

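### The main complete-case analysis of 12-month cholesterol makes no use of the 6-month value, so participants lost after month 6 are dropped, with avoidable bias if that loss relates to 6-month response differently by arm

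*Protocol article*

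**What the plan says.** All references are to the protocol article.

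- **Outcome** (Measures): "The primary outcome measure is total cholesterol at 12-month follow-up".
- **6-month measurement** (Measures; Table 1 under Follow-up assessments): "The blood test will be repeated at 6 and 12-month follow up by a clinical research network nurse".
- **Primary model** (Statistical analysis): a "linear random effects regression model adjusting for the baseline cholesterol, whilst accounting for clustering as a random effect (GP practice"). It names no 6-month term and no participant-level repeated-measures structure.
- **Analysis set** (Statistical analysis): "All analyses will be on an intention-to-treat basis", and later in the same section "Complete case analyses will be the main analyses from this study". Intention-to-treat is not defined further.
- **Missing data** (Statistical analysis): the plan will look into bias from missing data, and adds that "A supportive analysis will include adjusting for predictors of missingness that are related to outcome, if necessary".
- **Loss to follow-up** (Sample size inflation for clustering and attrition): "Dropout rates in the SMI trials are <20 % at 12 months". The calculation uses 20%.
- **Stopping the intervention** (Consent and research assessments): a participant who "no longer wishes to attend the intervention appointments, he/she will still be invited to attend the follow-up assessments".

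**The concern.** The complete-case choice is stated in the article, so it is not a detail left to the analysis plan. A participant seen at 6 months but not at 12 contributes nothing to the primary estimate, although the 6-month cholesterol is the best available predictor of the missing value. The supportive analysis adds covariates to the model for the same completers, so it does not bring these participants back.

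At stake is the treatment contrast. Complete-case analysis of covariance is safe if 12-month missingness is unrelated to the outcome given arm and baseline. The contrast also survives, approximately, when dropout depends on the 6-month value in the same way in both arms. It does not survive when that dependence differs by arm. Such a difference is possible here: participants and practice staff are unmasked (Blinding), and only the intervention arm has the 6-month series of appointments (Intervention arm). If intervention participants with poor 6-month cholesterol are the ones who miss the 12-month test, the benefit is overstated. If those with good values are, it is understated.

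**Working it through.** **1. The plan's own sample size, and what it implies for power.** Inputs from Effect size and Sample size inflation: difference 0.4 SD = 0.4 × 1.3 = 0.52 mmol/l, 90% power, 5% significance (two-sided assumed), ICC 0.02, 4 analysed per practice, 20% attrition.

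- Per arm before clustering: 2 × (1.960 + 1.282)² / 0.4² = 131.3, so 132. This matches.
- Design effect: 1 + (4 − 1) × 0.02 = 1.06; 132 × 1.06 = 139.9, so 140. This matches.
- Attrition: 140 / 0.8 = 175 per arm, 350 in total; 350 / 5 = 70 practices. This matches.
- Power with 140 analysed per arm: effective n = 140 / 1.06 = 132.1; 0.4 × √(132.1 / 2) − 1.960 = 1.29, which gives 90.2%.

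The trial is therefore already powered on completers. Power is not the issue.

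**2. Who is dropped.** At the planning figure, 0.20 × 350 = 70 leave and 280 remain. Only those lost after the 6-month visit have a usable 6-month value. The article does not give that share. If it is 25% to 100%, about 18 to 70 people are affected.

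**3. Size of the bias by simulation.** The setting is 1,500 trials per scenario, 70 practices of 5, SD 1.3, ICC 0.02 and 20% missing at 12 months. These inputs are assumptions, not in the article:

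- correlations baseline–6 months 0.5 to 0.7, baseline–12 months 0.45 to 0.6, 6–12 months 0.6 to 0.8;
- late dropout depending on 6-month cholesterol with log-odds 0.7 per SD (odds ratio about 2).

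Complete-case bias in mmol/l (and as % of 0.52) for the middle correlations (0.6, 0.5, 0.7):

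| Share of losses after month 6 | Same in both arms | Intervention arm only | Opposite by arm |
|---|---|---|---|
| 25% | −0.008 (1.4%) | −0.021 (4.0%) | −0.042 (8.1%) |
| 50% | −0.001 (0.3%) | −0.034 (6.5%) | −0.073 (14.0%) |
| 75% | 0.000 (0.0%) | −0.053 (10.1%) | −0.108 (20.9%) |
| 100% | 0.003 (0.6%) | −0.066 (12.8%) | −0.135 (25.9%) |

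Negative values overstate the benefit. Simulation error on each bias is about 0.136 / √1500 = 0.004. Across all three correlation sets the ranges are about 2–13% (one arm) and 7–26% (opposite). An estimator that also uses the 6-month value had bias within 0.01 mmol/l throughout. Its variance was about 1–10% lower, with ratios running from just under 1 down to 0.90.

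**4. Check by hand.** For dropout in one arm, the shift in that arm's baseline-adjusted 12-month mean is approximately

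SD × b × q × (r₆,₁₂ − r₀,₆ × r₀,₁₂),

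where b is the log-odds per SD and q is late losses divided by those still present at month 6. With the middle correlations the bracket is 0.7 − 0.6 × 0.5 = 0.40.

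- All losses late: q = 70 / 350 = 0.20; 1.3 × 0.7 × 0.20 × 0.40 = 0.073 (simulated 0.066; the approximation runs slightly high at larger q).
- A quarter late: q = 17.5 / 297.5 = 0.059; 1.3 × 0.7 × 0.059 × 0.40 = 0.021 (simulated 0.021).

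The formula also shows the pattern. Equal shifts cancel between arms, opposite shifts add, and the bias rises roughly in step with the late share.

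**The case against.** A fair defence has several parts.

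- **Intention-to-treat.** A reader might infer that complete-case analysis breaks the intention-to-treat promise. The article does not support that. Participants are compared by randomised arm, those who stop the intervention are still invited to follow-up, and non-adherence has its own supportive analysis. The label and the analysis set are left unreconciled, but this is not a per-protocol analysis. A joint model would itself leave out anyone with no post-baseline value. This objection stands.
- **Scale of loss.** A reader might take 20% as the expected loss and suppose that every dropout has a 6-month value. The 20% is a planning allowance at the top of the cited range, and early losses have no 6-month value. This also stands.
- **Mechanism.** The 12-month blood test is a research visit, reimbursed equally in both arms and separate from the intervention appointments. Nothing in the article shows that dropout will differ by arm, still less run in opposite directions. This stands as a limit on the size claimed. It gives no reason to rely on the stronger assumption when the data to weaken it are collected anyway.
- **Covariates.** A reader might infer that the supportive analysis will adjust for 6-month cholesterol and so remove part of the treatment effect. The article never names that variable. The wording is merely not confined to baseline variables, and which predictors enter is ordinary analysis-plan detail.
- **Existing provision.** Missing data are to be investigated, and N allows for loss. Both are true, but neither returns the excluded participants to the analysis.

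**Conclusion.** The point holds as an improvement to a stated analysis choice. The main analysis sets aside post-baseline cholesterol that the trial collects, and so rests on a stronger missing-data assumption than it needs to.

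The bias could be anywhere from zero to about 0.14 mmol/l against a target of 0.52. It is negligible if late dropout is random or depends on 6-month cholesterol alike in both arms. At the extreme of opposite dependence with all losses late, it is about as large as the standard error (0.135 against 0.136). The assumed correlations, the odds ratio of about 2 and the late share drive these figures, and none of them is in the article. They show what is possible and do not forecast this trial. The precision gain is small, and neither the required sample size nor the planned power changes.

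**What to change.** 1. State that participants are analysed in the arm to which their practice was randomised, and say which participants enter the main analysis.
2. Make the main analysis a likelihood-based linear mixed model of 6- and 12-month cholesterol, with arm by time, baseline cholesterol by time, a practice random effect, and a participant effect or unstructured residual covariance. Report the 12-month contrast as primary. Multiple imputation that includes the 6-month value and respects clustering by practice is an acceptable alternative.
3. Keep the complete-case model as a sensitivity analysis.
4. As a clarification, limit predictors of missingness entered as covariates to baseline variables. Use post-randomisation predictors only through the joint model or imputation.

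The cost is wording and a somewhat longer Stata model, with no new data, visits or participants. The limits should be stated. The joint model still assumes missing at random, so it does not protect against dropout that depends on the unseen 12-month value. It also excludes participants with no post-baseline measurement unless they are imputed.

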#### Economic evaluation

The aim of the economic evaluation is to report the mean incremental cost of the PRIMROSE intervention compared to treatment as usual in the reduction of CVD risk in people with SMI, from the NHS perspective in the primary analysis and from a societal perspective in a secondary analysis. The primary effectiveness outcome, as recommended by NICE, will be quality-adjusted life years (QALYs) [56]. Responses to the EQ-5D-5 L questionnaire collected during the trial will be used in conjunction with EQ-5D-5 L specific valuation sets [47] to calculate utility scores over a time horizon of 1 year. Baseline differences in utility scores will be adjusted for using regression analysis. The cost of the intervention will include the cost of the printed materials, training, clinical tests and other consumables used during the intervention and nurse/HCA time spent delivering the intervention. The cost-components that will be included in the health care perspective analysis for arms of the trial include new prescriptions during the study follow-up period, general and psychiatric hospital admissions, A&E contacts; outpatient visits, primary care contacts and community service use. Informal care arrangements, changes in living situation, carer costs, and out-of-pocket costs for services such as weight-management programmes, gym and leisure activities, smoking cessation and community service use [48] will be included in the societal perspective analysis. Unit costs will be obtained from the Personal Social Services Research Unit (PSSRU) [57], reference costs [58], British National Formulary (BNF) [59] and other national sources of costing information. Cost-effectiveness will be reported as the mean incremental cost per QALY gained of the PRIMROSE intervention versus treatment as usual. All cost-effectiveness analyses will conform to the recommended methodology [56]. Bootstrapping will be used to derive 95 % confidence intervals for mean cost and QALYs for the two trial groups, 95 % confidence intervals around the incremental cost-effectiveness ratios and cost-effectiveness acceptability curves and cost-effectiveness planes. The analyses will be subjected to one-way and two-way sensitivity analyses to test any assumptions made in the analysis. Trial results will also be used to update a long-run CVD cost-effectiveness model, extrapolating costs and consequences to a 10-year time horizon using discrete event-simulation.

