### Study objectives

The aim of the study is to test the clinical effectiveness and cost effectiveness of a behavioural intervention to lower CVD risk in primary care delivered to people with SMI.

The primary objective is to establish the effectiveness of the intervention in reducing total cholesterol over a 12-month period compared with treatment as usual (TAU).

The secondary objectives are to determine whether the intervention accomplishes the following:reduces glycated haemoglobin (HbA_1c_), blood pressure, body mass index (BMI), waist circumference, total cholesterol/HDL cholesterol ratio, HDL cholesterol, and LDL cholesterol;lowers cardiovascular risk scores;increases physical activity, improves diet, reduces the number of cigarettes smoked and reduces alcohol intake;increases the uptake of statin medications and adherence to statin regimens; andincreases satisfaction with services, wellbeing and quality of life.

We also aim to establish the cost-effectiveness of the intervention while considering both the costs of the intervention itself and other direct health care costs.

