Participants in the GP practices allocated to the intervention will be offered weekly to fortnightly appointments with the practice nurse/HCA over a period of 6 months. Progress with CVD risk reduction will be reviewed at each consultation. Appointments will decrease to monthly if satisfactory progress is made with reducing CVD risk. There will be flexibility over the delivery of the intervention depending on each individual’s preferences and needs; however, the intervention will include one or more of the following elements:Setting and monitoring participant-led behavioural goals aimed at lowering CVD risk (for example, improving adherence to statins or other CVD risk lowering medications, improving diet, increasing physical activity, reducing smoking and/or alcohol consumption.Use of a health plan to formulate a health goal and action plan and record progress with achieving the identified health goal.Sign-posting to services such as smoking cessation or physical activity programmes.Statin prescriptions to people whose CVD risk or lipids exceed recommended thresholds. The choice of statin will follow local and national treatment guidelines for statin prescribing. Current NICE guidance advises initial treatment with atorvastatin 20 mg unless there are drug interactions or contraindication [27]. Active monitoring of adherence to medication and response will be carried out.Prescription of other medications such as nicotine replacement therapy for smoking cessation, anti-hypertensives for raised blood pressure or metformin for diabetes and weight loss. Again active monitoring of adherence, side effects and response will be carried out.Involvement of carers and mental health key workers in monitoring adherence, supporting attendance at appointments and supporting a healthy lifestyle.

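### Read literally, drug costs cover only new prescriptions, so differences between arms in continuing, stopped or switched medication drop out of the incremental cost

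*Protocol article*

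**What the plan says.** The Economic evaluation section takes an NHS perspective in the primary analysis and reports incremental cost per QALY over one year. For both arms, it lists the health-care cost components as "new prescriptions during the study follow-up period, general and psychiatric hospital admissions, A&E contacts; outpatient visits, primary care contacts and community service use".

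The Economic measures section describes the drug data in matching terms: "medications used in the 12-months prior to baseline and any new prescriptions during the study follow-up period". Table 1, under Follow-up assessments, describes the same extraction differently. Its row reads "Prescribed medications", sourced from medical records at 0 and 12 months, with no restriction to new items.

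Four other places bear on the point:

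- **Exclusion criteria:** people already taking statins may enter if their lipids remain raised at screening.
- **Study objectives:** a secondary objective is that the intervention "increases the uptake of statin medications and adherence to statin regimens".
- **Intervention arm:** adherence to statins and other cardiovascular medication is a named behavioural goal, and adherence is actively monitored.
- **Treatment as usual arm:** nurses and healthcare assistants are not asked to check adherence or arrange statin prescriptions.

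**The concern.** A trial that sets out to change how people use drugs they already take needs a drug cost that can register that change. A component limited to newly started drugs cannot do so. If the intervention leads to more regular use of an existing statin, any benefit reaches the QALY through the EQ-5D-5L, but the extra prescriptions do not reach the cost. If one drug replaces another, the new one is charged in full and the saving on the stopped one is lost.

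At stake is the incremental cost, which is the numerator of the main economic result. Trial results also feed the 10-year model. The trial is described as ongoing, so if extraction follows the narrower wording, data on continuing drugs may not be collected and could be hard to recover later.

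**Working it through.** The document states no unit cost, drug cost, QALY difference or cost-effectiveness ratio, so there is no figure of the plan's own to reproduce on this point. The check has three steps.

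**1. What *new* most naturally means.** The Economic measures sentence sets drugs used before baseline against new prescriptions in follow-up. That contrast makes drugs first started during follow-up the natural reading. Table 1 carries no such limit. The article therefore describes the drug data in two ways and does not say which one is costed.

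**2. Whether the omitted part cancels between arms.** For the mean cost per participant over 12 months, write N for drugs started in follow-up and C for drugs already in use at baseline, with subscripts I (intervention) and T (treatment as usual).

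- Full incremental drug cost = (N_I - N_T) + (C_I - C_T)
- Literal incremental drug cost = N_I - N_T
- Error (literal minus full) = -(C_I - C_T)

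The error is zero only if C_I = C_T. The design gives no ground for assuming this, because continuing statin users are enrolled and only one arm is asked to work on adherence. The sign depends on what happens:

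- More regular use of existing drugs in the intervention arm makes C_I larger, so the literal increment is too low.
- More stopping or switching in the intervention arm makes C_I smaller, so the literal increment is too high. For one participant who switches at baseline from a drug costing *a* a year to one costing *b*, the true change is b - a. The literal rule records b, an overstatement of *a*.

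The two effects pull in opposite directions, so the net sign cannot be read from the document.

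**3. Illustration on assumed inputs.** Let D be the difference between arms (intervention minus usual care) in the share of participants using a continuing drug, and *a* its annual cost. Then C_I - C_T = D × a, and the error is -D × a. Both inputs are assumptions.

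| D | a = £20 | a = £50 | a = £200 |
|---|---|---|---|
| +0.10 | -£2 | -£5 | -£20 |
| 0 | £0 | £0 | £0 |
| -0.10 | +£2 | +£5 | +£20 |

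For example, 0.10 × £200 = £20. On these values the error per participant runs from -£20 to +£20. It grows in proportion if the difference in use is larger or the drugs are dearer.

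**The case against.** Three arguments on the other side deserve weight.

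- **The list is not closed.** The components are introduced as things the cost will include, and the section promises to follow recommended methodology. This carries limited force: prescriptions are on the list, and the list itself narrows them to new ones. A general promise does not override a specific definition.
- **The word may be loose.** It could mean any prescription issued after baseline, as opposed to medication used before it, and the Table 1 row is consistent with that. This stands as a possibility. It is a reason to reconcile the wording rather than to leave two descriptions in place.
- **Continuing drugs may cancel.** If their use is the same in both arms, leaving them out does no harm to the increment. That is correct, and it is why bias is possible but not shown.

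A reader might also infer that PRIMROSE appointments are charged twice in the intervention arm. Intervention cost includes "nurse/HCA time spent delivering the intervention", while "primary care contacts and community service use in the previous 12 months will all be collected from the medical records", and the appointments take place at the participant's own practice. The document does not support that stronger reading. It never says that these visits are counted as primary care contacts; it only does not say that they are excluded. The Intervention arm section has the nurse or healthcare assistant log attendance, and adherence to the appointments is collected at 12 months, so the visits can be separated. The rule for doing so is costing detail that a condensed article commonly leaves to a fuller plan. If the visits are separated, the overstatement is zero.

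**Conclusion.** The point holds for prescriptions. Two sections limit the drug cost to new prescriptions and Table 1 does not. Under the literal reading, changes in continuing, stopped or replaced drugs are left out of a comparison in which one arm is specifically asked to influence them. The incremental cost can be biased as a result.

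The size and direction cannot be derived from the document. The range of -£20 to +£20 per participant rests wholly on an assumed difference of up to 10 percentage points and assumed annual costs of £20 to £200, and it includes zero. No shift in the cost per QALY can be stated, because the document gives no QALY difference. The conclusion also assumes that *new* means newly started; if it means every prescription issued in follow-up, only the wording needs repair.

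The matter affects the economic evaluation and leaves the primary outcome, total cholesterol, untouched. It is worth correcting while data are still being collected. The overlap between appointments and primary care contacts merits no more than a clarifying sentence.

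**What to change.** **Main change.** In Economic measures and Economic evaluation, replace the reference to new prescriptions with all prescriptions issued during the 12-month follow-up, in both arms, so that both sections agree with Table 1. Keep the pre-baseline medication data as the baseline measure.

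**Minor clarification.** In Economic evaluation, state that PRIMROSE appointments, identified from the attendance log, are costed once under intervention delivery and are not also counted as primary care contacts.

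**Cost.** The main change is to wording. Prescribed medications are already listed for extraction at 12 months, so the extra extraction and costing work should be small. If the 12-month extraction was going to record only the drugs current at that visit, items issued across the whole year would have to be added. Including continuing drugs may somewhat widen the interval for cost, since more cost variation enters the total. The appointment clarification uses a log that is already planned.
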